## Abstract

**Introduction:**

Postoperative delirium (POD) and postoperative cognitive decline (POCD) can be observed after cardiosurgical interventions. Taken together, these postoperative neurocognitive disorders (PNCDs) contribute to increased morbidity and mortality. Preoperative risk factors of PNCD, such as decreased neuropsychometric performance or decreased cognitive daily activities, can be interpreted as reduced cognitive reserve. This study aims to build up cognitive reserves to protect against the development of PNCD through preoperative, home-based, cognitive training.

**Methods:**

The planned research project is a monocentric, two-arm randomized controlled intervention study involving 100 patients undergoing elective cardiac surgery with extracorporeal circulation. Patients will be assigned to a training group or control group. The intervention involves a standardized, paper-and-pencil-based cognitive training that will be performed by the patients at home for ~40 min per day over a preoperative period of 2–3 weeks. The control group will receive neither cognitive training nor a placebo intervention. A detailed assessment of psychological functions will be performed ~2–3 weeks before the start of training, at the end of the training, during hospitalization, at discharge from the acute clinic, and 3 months after surgery. The primary objective of this study is to investigate the interventional effect of preoperative cognitive training on the incidence of POD during the stay in the acute clinic, the incidence of POCD at the time of discharge from the acute clinic, and 3 months after surgery. Secondary objectives are to determine the training effect on objective cognitive functions before the surgery and subjective cognitive functions, as well as health-related quality of life 3 months after surgery.

**Discussion:**

Should it become evident that the use of our cognitive training can both reduce the incidence of POCD and POD and improve health-related quality of life, this intervention may be integrated into a standardized prehabilitation program.

## Introduction

Neuropsychological complications following cardiac surgery include postoperative delirium (POD), postoperative cognitive decline (POCD) (1), and dementia (2). Depending on age and evaluation methods, the frequency of POD after cardiac surgery varies between 14 and 50% (3). The prevalence of POCD is reported to be in the range of 28% between the first and fourth postoperative month and 22% between the sixth and 12th postoperative month (4). Postoperative cognitive improvement (POCI) can also be measured after surgeries but occurs about three to six times less frequently than POCD (5). POCD is more noticeable in objective psychometric assessments and often appears subclinically; nevertheless, patients and their relatives have reported a subjective decrease in patients' cognitive abilities in daily living after heart surgery (6). POD and POCD are related to a reduced quality of life, long-term cognitive decline, increased economic costs, and higher mortality (3).

Preoperative psychological risk factors for the development of POCD include depression (7, 8) and reduced neuropsychometric functions (9). Preexisting cognitive impairment may also contribute to the development of dementia (10). In addition, depression (11), preoperatively reduced objective cognitive functions (11), or reduced cognitive everyday activities such as reading, writing, solving crosswords, and playing computer games (12) could be linked to the development of POD. Furthermore, in a rat model, it was shown that a preoperative enrichment of activity opportunities can lower the rate of POCD (13). In summary, diminished neuropsychometric functions or reduced cognitive everyday activities can be declared as a lower cognitive reserve. In the classical sense, the term “cognitive reserve” refers to the adaptability of cognitive processes, which can help to explain the sensitivity of cognitive abilities or everyday functions in the context of physiological aging and pathological neurodegeneration of the brain. The cognitive reserve can be influenced, among other things, by general cognitive ability in early life (intelligence), education, occupation, physical activity, leisure activities, or social engagement (14). For example, it has been shown that increased cognitive or social leisure activities performed within a wide life span (childhood to adulthood) can reduce the risk of developing dementia (15, 16). Increasing the cognitive reserve through focused cognitive training may, therefore, be a potential intervention target to prevent postoperative neurocognitive dysfunctions.

The primary objective of this study is to investigate the interventional effect of preoperative cognitive training on the incidence of POD during the stay in the acute clinic, the incidence of POCD at the time of discharge from the acute clinic, and 3 months after surgery. Secondary objectives are to determine the training effect on objective cognitive functions before the surgery and subjective cognitive functions, as well as health-related quality of life 3 months after surgery.

## Methods and analysis

### General conditions

The planned research project is a monocentric, randomized controlled study conducted by the Heart and Brain Research Group—a cooperation project between the Department of Cardiac Surgery of the Kerckhoff Heart and Thoracic Center in Bad Nauheim and the Department of Neurology of the University Hospital Giessen. Our working group consists of members of the Departments of Neurology, Neuropsychology, Radiology, and Cardiac Surgery who are responsible for the study procedure, including preparing the protocol, monitoring the study, and writing the study reports. This study protocol follows the Standard Protocol Items: Recommendations for Interventional Trials (SPIRIT) guidelines (17). The data monitoring committee was not believed to be necessary, as no adverse effects of cognitive training are expected.

### Trial registration

The study is prospectively registered with ClinicalTrials.gov (Identifier: NCT04493996. First posted: July 31, 2020. First patient enrolled: August 14, 2020).

### Dissemination policy

Our aim is to make the study results available to the public, healthcare providers, and scientists by publication in the public press, at scientific congresses, and as original articles in peer-reviewed journals. The results will be reported regardless of the size and direction of the effect.

### Recruitment

A study coordinator will receive information from the Department of Cardiac Surgery of the Kerckhoff Heart and Thoracic Center in Bad Nauheim about planned elective cardiac surgeries. After screening inclusion and exclusion criteria, patients will be informed in detail about the purpose and procedure of the study project.

### Inclusion criteria

- Elective cardiac surgery (on pump)° Coronary artery bypass surgery (CABG)° Aortic valve replacement (AVR)° Mitral valve replacement/reconstruction (MVR)° Combination surgery (CABG+AVR, CABG+MVR, AVR+MVR, CABG+AVR+MVR)

- Age > 18 years- Good knowledge of the German language (cognitive training and neuropsychological tests are language-dependent).

### Exclusion criteria

- Preexisting psychiatric disorders (depression and dementia) with acute clinical symptoms can impair psychological performance.- Preexisting neurological disorders (stroke, Parkinson's disease, and multiple sclerosis) with acute clinical symptoms can impair psychological performance.

### Randomization

Randomization will be implemented using a computer-generated randomization list (www.randomization.com) with a 1:1 blocked allocation ratio and block sizes of 10. The randomization list will be generated, sequentially numbered, and concealed before the start of the study by the randomization list holder, who is located in the department of Neurology at the University Hospital Giessen and Marburg. After recruitment and the first preoperative neuropsychological examination, a study coordinator will allocate patients to the cognitive training or control group. A study coordinator will inform the psychological training supervisor about which patients should be trained.

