### Power and sample size estimation

Because there are currently no effect sizes for extensive paper-and-pencil-based preoperative cognitive training in cardiac surgical patients using extracorporeal circulation, and because their influence on the incidence of POD and POCD is unclear, we have estimated sample size based on the effect sizes of general cognitive training in older healthy individuals, which ranges between d = 0.4 and d = 0.9 (20, 21). To not underestimate or overestimate the required sample size, we use an average value of d = 0.65. To find an effect size of d = 0.65 at a test power of 0.8 (alpha = 0.05) within an ANCOVA, a sample size of 77 subjects is required. With an estimated dropout rate of 23% in the preoperative test phase, the total sample size will be 100 subjects. The sample size per group is thus 50 patients. We used the analysis software G^*^Power-3 to calculate the sample sizes and the statistical power (22). We want to note that the power analysis refers to our secondary outcome “Changes from baseline neuropsychological parameters at the end of cognitive training.” Accordingly, the primary outcomes regarding the incidence of POD and POCD will be calculated exploratively.

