## Trial status

The study is currently enrolling patients. This study is registered with ClinicalTrials.gov (Identifier: NCT04493996. First posted: July 31, 2020. The first patient was enrolled on August 14, 2020). Recruitment is expected to be completed in November 2023. Protocol version: 1.0 (17-01-2022).

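### A fixed, published block size of 10, with a coordinator role at both entry and allocation, makes some upcoming assignments predictable; the running sequence should be kept from anyone who screens or enrols

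*Protocol article*

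**What the plan says.** All of this is in the protocol article.

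- **Randomization:** a computer-generated list, "with a 1:1 blocked allocation ratio and block sizes of 10". The list holder prepares, numbers and conceals it before the study starts. After recruitment and the first neuropsychological examination, "a study coordinator will allocate patients to the cognitive training or control group". A study coordinator also tells the training supervisor whom to train.
- **Recruitment:** "A study coordinator will receive information from the Department of Cardiac Surgery" about planned elective operations. Screening comes in the next sentence, in the passive, with no person named.
- **Inclusion and exclusion criteria:** patients need good German. Psychiatric and neurological disorders exclude when present "with acute clinical symptoms can impair psychological performance". Neither criterion has a scale or cut-off.
- **General conditions:** "The planned research project is a monocentric, randomized controlled study". No stratification factor is given anywhere.
- **Power and sample size estimation:** "the total sample size will be 100 subjects" and "The sample size per group is thus 50 patients".
- **Blinding:** outcome assessors are blinded. The list and its holder sit at another institution and take no part in training or outcome evaluation.
- **Trial status:** "The study is currently enrolling patients", so the block size became public while assignments were still unused.

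**The concern.** Concealing a list stops anyone looking up the next assignment. It does not stop someone who has seen the earlier ones from working it out when the block length is constant and known. Here one unstratified list runs at one site, so the count within a block is easy to keep, and the coordinator role sees every result. The same role title appears where candidates enter the trial, under criteria that need judgement.

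If the expected arm influenced who was entered, or when, the groups could differ at baseline in cognitive ability or motivation. The Introduction links low preoperative cognitive function to both POD and POCD. The planned POD and POCD comparisons are unadjusted chi-square or Fisher tests, so they would not correct such an imbalance.

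**Working it through.** **Inputs.** Block of 10, so m = 5 per arm (Randomization); 100 patients, 50 per arm, 23% dropout on 77 (Power and sample size estimation); one site (General conditions). Assumption for the calculation: all earlier assignments and the block size are known, and the next patient's place in the sequence is known.

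**1. The plan's own figures.** The article gives no figure for predictability. Its sample size is consistent: 77 / (1 − 0.23) = 100, and 100 / 10 = 10 complete blocks of 5 + 5, which gives 50 per arm.

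**2. Assignments certain in advance.** Once one arm is used up within a block, the rest is determined. The expected number of determined places is 2m / (m + 1) = 10 / 6 = 1.67 per block. That is 16.7%, or about 17 of 100 patients.

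**3. Best guess.** Always guess the arm with more places left, scoring ties as one half. The expected number correct is m + ½ × (4^m / C(2m, m) − 1) = 5 + ½ × (1024 / 252 − 1) = 6.53 of 10, or 65.3%, against 50% by chance. Enumerating all 252 possible block sequences gives the same 1.67 and 6.53. In 38.7% of assignments the favoured arm has probability of at least 2/3.

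**4. Ceiling on imbalance.** Let D be the difference in mean prognosis between patients entered when training is expected and those entered when control is expected. The expected between-arm difference is then at most (2p − 1) × D = (2 × 0.653 − 1) × D = 0.306 × D. The documents give no value for D. As an assumed range, D = 0.2, 0.5 and 0.8 SD gives at most 0.061, 0.153 and 0.245 SD in the steered characteristic. The documents do not allow this to be converted into POD or POCD incidence.

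**5. Effect of changing the block size.** The first two rows are exact. The last two are simulated (2,000 trials of 100 patients) with an optimal guesser who knows the set of sizes but not their order; the sets are illustrative assumptions.

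| Blocks | Certain | Best guess right |
|---|---|---|
| Fixed 10 (plan) | 16.7% | 65.3% |
| Fixed 4 | 33.3% | 70.8% |
| Varied 6/8/10 | 1.6% | 66.3% |
| Varied 4/6/8 | 2.3% | 67.9% |

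Varying the block size removes nearly all certainty but leaves the average hit rate no lower. Only withholding the running sequence removes the information that guessing relies on.

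**The case against.** The case on the other side is substantial, and most of it stands as a limit on the point.

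- **Who screens.** A reader might infer that one person both screens and allocates. The article does not say so. The screener is unnamed, and the indefinite article leaves room for different coordinators. What stands is that nothing in the text separates the two tasks.
- **Existing safeguards.** The list is concealed off site, and allocation already follows consent and baseline testing. This prevents look-up and fixes the order of steps. It does not prevent deduction from past assignments.
- **Predictability is a ceiling.** A full baseline assessment lies between screening and allocation. With several patients pending, nobody at screening knows which place a candidate will take. Entry time is also limited, since baseline testing falls 2–3 weeks before an elective operation. A fixed block of 10 is also less predictable than smaller fixed blocks.
- **Comparison with the planned effect.** It is tempting to set a baseline shift of about 0.15 SD against the planned d = 0.65. That does not hold. The article ties d = 0.65 to the ANCOVA of neuropsychological change at the end of training, which has the preoperative value as a covariate and so adjusts for the imbalance in question.
- **Randomisation as the only protection.** This also goes too far. Assessors are blinded, the ANCOVAs adjust, and POCD is a within-patient change, so a baseline difference does not carry straight into it. POD has no such baseline element. The article also calls the POD and POCD analyses explorative.
- **Actual steering.** Nothing in the documents shows that it occurred.

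**Conclusion.** The point holds as a moderate, avoidable weakness in how assignments are released, not as a demonstrated bias. With the published fixed block and knowledge of past assignments, up to 16.7% of assignments are certain in advance and a best guess is right up to 65.3% of the time. Harm would require that someone involved in entry sees the running sequence, knows the candidate's place in it, and acts on it. The article leaves the first of these open and gives no evidence of the last. The exposed results are mainly the unadjusted POD and POCD incidence comparisons, POD most directly. The ANCOVA outcomes are largely protected against imbalance in the test scores themselves. The sample size is not affected.

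**What to change.** **Main change, for patients not yet allocated.** Once consent and baseline testing are recorded as complete, the off-site list holder releases the single assignment directly to the training supervisor, who mails the training package or the control letter. No one who screens or enrols sees the running sequence. This works whatever the block size and uses roles that already exist; the supervisor is already outside outcome evaluation.

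**Second measure.** Regenerate the unused part of the list with randomly varied block sizes and do not disclose them. In the illustrative sets above, this cuts certain assignments from 16.7% to about 2%. It should not be the only change, because the overall guess rate stays at about 66–68%.

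**Cost.** A short amendment, which the article says must go to the Ethics Committee; the supervisor takes over the allocation mailing; and arm sizes may differ slightly if the last block is incomplete. The change cannot reach patients already allocated. Recruitment was expected to end in November 2023, so its value depends on how many assignments remain.

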### Blinding

Neuropsychologists and nursing staff who will be involved in the assessment of outcome variables will be blinded for randomization status. The training sessions will be conducted by a psychological training supervisor who is not involved in the evaluation of outcome parameters to ensure blinding. The holder of the randomization list is not involved in the supervision of the training or the evaluation of all examinations on neuropsychometrical functions and delirium. In addition, the randomization list and its holder are located in the department of Neurology at the University Hospital in Giessen where the psychological evaluations, the intervention, and the surgery do not take place. Furthermore, when we inform patients by mail about which randomization group they are assigned to, we instruct them for all subsequent assessments not to inform the investigators about their randomization status.

### Study process

After we obtain written consent from the patients, a detailed neuropsychometric assessment will be carried out 2–3 weeks preoperatively, and the patients will provide other information *via* questionnaires. These questionnaires, which must be completed by the patients themselves, refer to depression, anxiety, health-related quality of life, cognitive and social activities in everyday life, and questions on cognitive failures in everyday life. In addition, close relatives will also assess cognitive failures in the patients' everyday life in a separate questionnaire. Following neuropsychological assessment, randomization into a cognitive training group or control group will be performed. Patients in the training group will receive a package with the training material by mail. Those in the control group will receive a letter stating that they will not be involved in a training program. The control group will receive neither cognitive training nor placebo intervention. A second detailed neuropsychometric status assessment will be performed when patients are admitted to the acute clinic, which usually is scheduled 1 day before surgery. In addition, patients will complete questionnaires on depression, anxiety, and recent cognitive and social activities. At the time of discharge from the acute clinic, a short cognitive screening test (MOCA) will be carried out. Three months after surgery, all patients will be included in a final examination, which will take place at the Kerckhoff Clinic in Bad Nauheim, Germany, or at the patients' homes if required. This examination will include a further detailed neuropsychometric assessment, as well as questionnaires on depression, anxiety, health-related quality of life, questions on cognitive failures in everyday life, and recent cognitive and social everyday activities.

Baseline demographics and characteristics will include age, gender, years of educational and occupational background, body mass index, preexisting medical conditions (arterial hypertension, diabetes mellitus, dyslipidemia, and severity partition for left ventricular ejection fraction [defined by Lang et al. (18)]), heart failure, renal insufficiency (defined by a creatinine value above the in-house norms (men: >1.2 mg/dl, women: >0.9 mg/dl)), preoperative medication, type of surgery (CABG, AVR, MVR, and combination surgery), anesthesia and analgesics administered (type, amount, and duration), duration of the operation, duration of extracorporeal circulation, cross-clamp time, lowest body temperature, invasive ventilation time, peri- and postoperative complications (delirium, arrhythmia, atrial fibrillation, renal insufficiency, acute blood loss anemia, transient ischemic attack, stroke, dysarthria, aphasia, and death), days on the intensive care unit, and the total length of stay on the normal ward. We plan no systematic and standardized pre- or postoperative neuroradiological imaging.

The study process is shown in Figure 1. A detailed trial schedule according to the SPIRIT guidelines for study protocols is shown in Table 1 (17).

**Figure 1 F1:**
[figure not shown]
Timeline of the study-related events. The first examination includes neuropsychological tests and questionnaires before randomization and training. After the preoperative training period, neuropsychological tests and questionnaires will be administered a second time on admission to the acute clinic. After the surgery, daily delirium screenings will be performed and, on discharge from the acute clinic, neuropsychological screening will be carried out. To determine the long-term effects of cognitive training, neuropsychological tests and questionnaires will be carried out 3 months after surgery. MOCA, Montreal Cognitive Assessment; HADS, Hospital Depression and Anxiety Scale; LEQ-D, Lifetime of Experiences Questionnaire; CAS, Cognitive Activity Scale; CFQ, Cognitive Failure Questionnaire; SF-36, 36-Item Short Form Health Survey; ICDSC; Intensive Care Delirium Screening Checklist; CAM, Confusion Assessment Method.

**Table 1 T1:** Study plan for recruitment, interventions, and investigations.

**Time point**	** *t_0_* **	** *t_1_* **	** *t_2_* **	** *t_3_* **	** *t_4_* **	** *t_5_* **	** *t_6_* **	** *t_7_* **	** *t_8_* **
**Recruitment**
Inclusion criteria	X								
Informed consent	X								
Randomization		X							
**Interventions**
Surgery					X				
Cognitive training			X						
**Assessments**
MOCA	X			X				X	X
BVMT-R	X			X					X
VLMT	X			X					X
TMT	X			X					X
LNS	X			X					X
SKT-7	X			X					X
RWT	X			X					X
CFQ	X								X
LEQ-D	X								
CAS	X			X					X
HADS	X			X					X
SF36	X								X
ICDSC						X			
3-CAM							X		

MOCA, Montreal Cognitive Assessment; BVMT-R, Brief Visuospatial Memory Test-Revised; VLMT, Verbaler Lern- und Merkfähigkeitstest (Auditory Verbal Learning and Memory Test); TMT, Trail Making Test; LNS, Letter Number Span; SKT, Syndrom-Kurztest Test (Short Performance Test); RWT, Regensburger Wortflüssigkeits-Test (Regensburger Word Fluency Test); CFQ, Cognitive Failure Questionnaire; LEQ-D, Lifetime of Experiences Questionnaire; CAS, Cognitive Activity Scale; HADS, Hospital Depression and Anxiety Scale; SF-36, 36-Item Short Form Health Survey; ICDSC, Intensive Care Delirium Screening Checklist; CAM, Confusion Assessment Method.

